# Is diverting loop ileostomy necessary for completion proctectomy with ileal pouch-anal anastomosis? A multicenter randomized trial of the GETAID Chirurgie group (IDEAL trial): rationale and design (NCT03872271)

**DOI:** 10.1186/s12893-019-0657-7

**Published:** 2019-12-12

**Keywords:** Pouch-anal anastomosis, Ileostomy, Ulcerative colitis, Staged IPAA, Modified 2-stage IPAA

## Abstract

**Background:**

There is no quality evidence of the benefit of defunctioning ileostomy (DI) in ileal pouch-anal anastomoses (IPAAs) performed for inflammatory bowel disease (IBD), but most surgical teams currently resort to DI. In the case of a staged procedure with subtotal colectomy first, completion proctectomy with IPAA is performed for healthy patients, namely, after nutritional support, inflammation reduction and immunosuppressive agent weaning. Therefore, the aim of this trial is to assess the need for systematic DI after completion proctectomy and IPAA for IBD.

**Methods/design:**

This is a multicenter randomized open trial comparing completion proctectomy and IPAA without (experimental) or with (control) DI in patients presenting with ulcerative colitis or indeterminate colitis. Crohn’s disease patients will not be included. The design is a superiority trial. The main objective is to compare the 6-month global postoperative morbidity, encompassing both surgical and medical complications, between the two groups. The morbidity of DI closure will be included, as appropriate. The sample size calculation is based on the hypothesis that the overall 6-month morbidity rate is 30% in the case of no stoma creation (i.e., experimental group) vs. 55% otherwise (control group). With the alpha risk and power are fixed to 0.05 and 0.80, respectively, and considering a dropout rate of 10%, the objective is set to 194 patients. The secondary objectives are to compare both strategies in terms of morbi-mortality at 6 months and functional results as well as quality of life at 12 months, namely, the 6-month major morbidity and unplanned reoperation rates, 6-month anastomotic leakage rate, 6-month mortality, length of hospital stay, 6-month unplanned readmission rate, quality of life assessed 3 and 12 months from continuity restoration (i.e., either IPAA or stoma closure), functional results assessed 3 and 12 months from continuity restoration, 12-month pouch results, 12-month cost-utility analysis, and 12-month global morbidity.

**Discussion:**

The IDEAL trial is a nationwide multicenter study that will help choose the optimal strategy between DI and no ileostomy in completion proctectomy with IPAA for IBD.

**Trial registration:**

ClinicalTrial.gov: NCT03872271, date of registration March 13th, 2019.

## Background

Ulcerative colitis (UC) is a colonic inflammatory bowel disease (IBD) that occurs in young adults. This life-long disease is of public health significance. Indeed, UC prevalence surpasses 0.5% in Europe and is increasing in newly industrialized countries [1]. The proportion of UC patients requiring surgery ranges from 10 to 30% according to the extent of the disease [2, 3]. Restorative proctocolectomy with ileal pouch-anal anastomosis (IPAA) is the gold standard surgery in familial adenomatous polyposis (FAP), UC, and IBD unclassified (IBDU), another colonic IBD formerly called indeterminate colitis [4]. Indeed, this procedure is the only treatment that eliminates both inflammatory and oncologic risks in the colonic and rectal segments. IPAA is a complex procedure, is mostly performed in two or three stages in cases of colonic IBD, and includes a defunctioning ileostomy to avoid anastomotic leakage [4, 5]. In the “traditional” two-stage IPAA, restorative proctocolectomy with IPAA is diverted by an ileostomy, and the second stage is ileostomy closure. In the three-stage IPAA, primary subtotal colectomy (STC) is performed with either end ileostomy or double-end stoma (i.e., ileo-sigmoidostomy). The second stage is the completion of proctectomy with IPAA. The pouch is diverted by a defunctioning ileostomy, which is closed in the third stage 6 to 8 weeks later. In the three-stage IPAA, STC allows the patient to recover from inflammation, malnutrition and immunosuppressive medication. The second stage is usually performed 2 or 3 months later, with the patient in good health. Therefore, the need for a systematic defunctioning ileostomy is questioned, and the “modified” two-stage IPAA has been developed, where STC is followed by completion proctectomy and IPAA, without defunctioning ileostomy.

Indeed, defunctioning ileostomy has several drawbacks, including specific complications (ileostomy prolapse, parastomal hernia, skin erosions), small bowel obstruction (SBO) that occurs in 18 to 22% of the patients [6–8] and dehydration that may require readmission. Defunctioning ileostomy has also associated with negative psychological impacts and a poor quality of life (QoL) before closure [9]. Moreover, stoma closure requires a third surgical procedure under general anesthesia and is associated with a 4% risk for anastomotic leakage. Overall, during the ileostomy period, 8% of patients will require reoperation [10].

An old randomized study from 1992 included 45 patients with no corticosteroid treatment and compared systematic ileostomy during IPAA and no ileostomy. Half of the patients in each group had STC, and the postoperative morbidity was 52% in the “ileostomy” group vs. 32% in the “no ileostomy” group (including an SBO incidence of 22% in the “ileostomy” group vs. 9% in the “no ileostomy” group). These differences were not significant, but the number of patients was small, and these results did not take into account the morbidity of ileostomy closure. Moreover, the mean hospital length of stay (LOS) was significantly longer in the “ileostomy” group than in the in the “no ileostomy” group when both IPAA and ileostomy closure were assessed [6].

More recently, some retrospective case-controlled studies have assessed one-stage IPAA (i.e., total proctocolectomy and IPAA without ileostomy) [11, 12]. The morbidity was comparable between patients who underwent one-stage and those who underwent traditional two-stage IPAA. However, the majority of the patients had FAP, not IBD; all IBD patients were carefully selected, and none received corticosteroid medication. Thus, these results cannot be extended to all colonic IBD patients. Interestingly, a retrospective study emanating from international tertiary care centers found that a “modified” two-stage procedure might be the best option for IBD patients who are at high risk for postoperative morbidity [7]. Namely, Sahami et al. compared 305 IBD patients undergoing IPAA with defunctioning ileostomy to 316 patients undergoing IPAA without defunctioning ileostomy. The rate of anastomotic leakage was not influenced by the ileostomy (ileostomy 16.7% vs. no ileostomy 17.1%, *p* = 0.92), but the ileostomy group presented with more SBO in the long term than the no ileostomy group (ileostomy 18.9% vs. no ileostomy 10.3%, *p* = 0.003). Defunctioning ileostomy was an independent risk factor for SBO (OR = 2.58 CI_95%_[1.5–4.7]). Moreover, the risk of pouch failure over time was similar between the two groups in the Kaplan-Meier analysis.

Two studies compared traditional and modified two-stage IPAA. In 2017, Samples et al. published a comparative nonrandomized prospective study including 248 patients [13]. Despite having patients with more aggressive disease in the modified two-stage group, the 3-year pouch failure rate was similar between the two groups. In their monocenter retrospective study, Zittan et al. included 459 patients [8]. Again, the patients undergoing a modified two-stage IPAA presented with more aggressive disease than those undergoing traditional IPAA, as expected by the indications for primary STC. However, the surgical short-term complications were comparable between the two groups, and the modified two-stage IPAA was an independent protective factor for postoperative fistula (OR = 0.27 IC_95%_[0.12–0.57]) [8].

### Objectives

Based on the abovementioned studies, the overall 6-month morbidity rate may be 55% in cases of ileostomy creation vs. 30% in cases of completion proctectomy with IPAA [6–8, 11–13]. Therefore, we hypothesized that in IBD patients who have had STC, completion proctectomy with IPAA could be performed without defunctioning ileostomy. The aim of the IDEAL trial was to compare IBD patients undergoing completion proctectomy and IPAA with and without defunctioning ileostomy. IDEAL is the French acronym for “diverting loop ileostomy in completion proctectomy with ileal pouch anal-anastomosis”.

## Methods and design

The IDEAL trial is a nationwide prospective, multicenter, open-label, randomized controlled trial in which IBD patients scheduled for completion proctectomy and IPAA will be randomized between having a defunctioning ileostomy (the ‘ileostomy’ strategy) and not having a defunctioning ileostomy (the ‘no ileostomy’ strategy). The study cannot be blinded because the presence of a stoma cannot be simulated and is obvious to both patients and practitioners. The study duration will be 48 months, and the recruitment duration will be 33 months. The study design is summarized in Fig. 1.

**Fig. 1 Fig1:**
[figure not shown]
Flow chart of the IDEAL trial *Defunctioning ileostomy, CR: continuity restoration

The list of randomization will be established before the implementation of the study with a 1:1 allocation ratio. It will be elaborated under the responsibility of the Clinical Research Platform, Assistance Publique – Hôpitaux de Marseille (APHM). A computer-generated randomized list will be drawn up using a permuted block design. Two stratification indicators will be retained: the center and the body mass index (< or ≥ 25 kg/m^2^).

This trial is supported by a grant from the French Ministry of Health (PHRC-18_0764).

### Endpoints

The primary endpoint is the 6-month global postoperative morbidity, i.e., the number of patients who develop at least one complication at the 6-month follow-up, encompassing both surgical and medical complications, as well as the morbidity of ileostomy closure. The 6-month timepoint is defined from the completion proctectomy and is therefore the same in both groups. We chose a 6-month endpoint because half of the patients will undergo ileostomy closure 6 to 12 weeks after IPAA. Therefore, a one-month or 3-month endpoint would be too short to correctly assess the morbidity of completion proctectomy +/− ileostomy closure. Moreover, a significant part of morbidity related to defunctioning ileostomy occurred in the long-term (i.e., after 30 days) in previously published studies [7, 8].

The secondary endpoints are as follows: 6-month major morbidity based on the Clavien-Dindo classification, [14] i.e., number of patients who develop at least one major complication at the 6-month follow-up; 6-month unplanned reoperation rate, i.e., any unplanned abdominal surgery, whether urgent or elective, other than ileostomy closure; 6-month anastomotic leakage rate assessed by a CT scan with an iodine injection, i.e., pelvic abscess, pelvic extradigestive air, pelvic free fluid or pelvic infiltration; 6-month mortality (linked or not with the disease); initial and cumulative 6-month length of hospital stay; 6-month unplanned readmission rate, i.e., other than for ileostomy closure; global and digestive quality of life (QoL) assessed by the Cleveland Global Quality of Life (CGQL) score [15] and the EuroQol Five-levels (EQ-5D-5 L) (i.e., utility values for health states) [16] at baseline and 3 and 12 months from continuity restoration (i.e., either IPAA or ileostomy closure); functional results assessed by the Cleveland Pouch Functional score (PFS) 3 and 12 months from continuity restoration [15]; 12-month pouch results: pouch failure (i.e., with definite ileostomy), anastomotic stricture, pouch in place, and repeat IPAA 12 months from continuity restoration; 12-month global morbidity (i.e., the number of patients who develop at least one complication 12 months from continuity restoration); and 12-month cost-utility analysis, performed 12 months from continuity restoration (cf. *‘* Economic assessment’ below). Though many redo-IPAAs are performed after one year, it is a secondary endpoint and it was felt not relevant enough in this trial to extend its follow-up.

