#### Intervention

An anesthesia consultation is planned before the surgery according to the habits of each department. Participation in the study will not alter the anesthetic procedures. The technical modalities of IPAA are not restricted, but it is mandatory that these modalities are identical in both groups for each center in terms of the type of approach (laparoscopic, single-port, robotic), type of anastomosis (hand-sewn or stapled), pelvic drainage and pouch drainage. Open surgery can be the chosen surgical approach for some patients, provided that a mini-invasive approach cannot be performed due to the surgical history or medical contra-indications, as estimated by the surgeon in charge. A J-pouch will be mandatory as it is the pouch of reference [18].

The defunctioning ileostomy is a covering loop ileostomy, which can be fashioned either in the right or left iliac fossa. The use of an ostomy rod is not mandatory and left to the surgeon’s judgment. Ileostomy closure will be performed 6 to 12 weeks after IPAA as per local protocol or later in case of pelvic sepsis. During stoma closure, the type of ileo-ileal anastomosis (whether end-to-end or side-to-side, hand-sewn or stapled) is not restricted. A CT enema scan can be performed before ileostomy closure to assess the absence of anastomotic leakages, as per the local protocol.

The patients randomized in the experimental group will be treated by completion proctectomy and the creation of an IPAA without a defunctioning ileostomy, which corresponds to a modified two-stage IPAA. As defunctioning ileostomy is omitted in this group, an anastomotic leakage test can be performed when deemed necessary by the surgeon in charge. However, the anastomotic leakage test will not be mandatory.

No concomitant care and interventions are prohibited during the trial.

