#### Patient safety

A safety analysis will be performed by an independent monitoring committee based on the anastomotic leakage rate in the experimental group (i.e., “no ileostomy” group): the chosen threshold will be 15%, as it represents a 30% higher rate of anastomotic leakage compared to the available rates in the literature for cases of completion proctectomy with ileostomy (8 to 16%) [7, 8, 12]. The management of amendments to the protocol and adverse events will follow the procedures of the regulatory department of the sponsor.

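### Pelvic free fluid or infiltration alone on CT counts as an anastomotic leak, which can distort the leak comparison between arms and leaves the definition behind the 15% safety threshold unclear

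*Protocol article*

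**What the plan says.** Under Endpoints, the 6-month leakage rate is a secondary endpoint, "assessed by a CT scan with an iodine injection, i.e., pelvic abscess, pelvic extradigestive air, pelvic free fluid or pelvic infiltration". The list is introduced as the meaning of the term, and its last two items are joined by 'or'. No contrast extravasation, anastomotic defect, sepsis or exclusion of another cause is required.

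Under Patient safety, an independent committee reviews safety "based on the anastomotic leakage rate in the experimental group" against a threshold of 15%. The article describes this as 30% above published rates of 8 to 16% with an ileostomy. That section neither repeats the CT list nor gives another definition.

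The Background reports small bowel obstruction by arm in two earlier studies. It was 18.9% with and 10.3% without ileostomy in a large retrospective comparison (long-term figures), and 22% against 9% in a 45-patient randomised study from 1992, whose differences were not significant.

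The Discussion treats the leak rate without a stoma as a main uncertainty and points to the leak endpoint among those meant to address it.

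**The concern.** Every participant has just had the rectum removed and a pouch formed. Fluid or infiltration in that pelvis need not come from the anastomosis, and obstruction can itself produce free fluid. Under the definition as written, such a patient with a sound anastomosis is recorded as a leak.

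The two consequences fall in different arms:

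1. **Between-arm comparison.** If obstruction is more frequent with an ileostomy, fluid due to obstruction adds more false leaks to the ileostomy arm. That favours omitting the ileostomy on the very endpoint meant to test whether omission is safe.
2. **Safety threshold.** In the no-ileostomy arm, ordinary postoperative findings, plus that arm's own smaller share of obstruction, would count towards 15% if the committee uses the same definition.

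The issue is how a scan is scored, not who is scanned. It would remain if CT were scheduled identically in both arms. The optional pre-closure scan ("A CT enema scan can be performed before ileostomy closure to assess the absence of anastomotic leakages, as per the local protocol"), which only the ileostomy arm can have, is a separate matter.

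**Working it through.** **The plan's own threshold.** Taking 30% above the quoted range gives 1.3 x 8% = 10.4%, 1.3 x 12% (midpoint) = 15.6% and 1.3 x 16% = 20.8%. A threshold of 15% is 30% above 15/1.3 = 11.5%, a rate the article does not state. It also lies inside the quoted 8 to 16% range, so there is little room for false leaks.

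**Consequence 1: between-arm comparison.** Obstruction rates are from the Background. Assumed, because the article gives neither: a true leak rate L = 10% in both arms, and a share f of obstructed patients who are scanned and show pelvic fluid without a leak, equal in both arms and unrelated to true leakage.

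Spurious gain in an arm = (1 - L) x obstruction rate x f.

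Spurious difference = 0.9 x (18.9 - 10.3) x f = 0.9 x 8.6 x f, or 0.9 x (22 - 9) x f = 0.9 x 13 x f.

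| f | Ileostomy / no ileostomy gain (18.9 vs 10.3) | Difference | Ileostomy / no ileostomy gain (22 vs 9) | Difference |
|---|---|---|---|---|
| 20% | 3.4 / 1.9 | 1.5 | 4.0 / 1.6 | 2.3 |
| 40% | 6.8 / 3.7 | 3.1 | 7.9 / 3.2 | 4.7 |
| 60% | 10.2 / 5.6 | 4.6 | 11.9 / 4.9 | 7.0 |

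All entries after f are percentage points. The between-arm difference is the relevant quantity, not the gain in one arm. Varying f over 10-50% and L over 8-12%, with the 18.9/10.3 rates only, gives differences of about 0.8 (0.88 x 8.6 x 0.10) to 4.0 (0.92 x 8.6 x 0.50) points. The sign is the same throughout.

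**Consequence 2: no-ileostomy arm.** With 194 patients allocated 1:1 there are 97 in this arm. The smallest count above 15% is 15, since 0.15 x 97 = 14.55. A single look at all 97 is a simplification; the article gives no denominator or schedule.

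- Share of leak-free patients falsely scored that brings the observed rate to 15%, (0.15 - L)/(1 - L): 7.6% at L = 8%, 5.6% at 10%, 3.4% at 12%.
- Exact binomial chance of at least 15 of 97 with no false leaks: 0.010 at 8%, 0.059 at 10%, 0.183 at 12%, and 0.71 at 17.1%, the no-ileostomy rate in the retrospective comparison.

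A few false leaks can therefore matter when the true rate is near 10%. At the only no-ileostomy leak rate the article reports, the threshold would probably be crossed without any.

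**The case against.** - **Clinical frequencies are absent.** The article does not say how often obstruction or normal healing gives pelvic fluid, nor when or why CT is done. Scan timing, reading rules and adjudication may stand in the full protocol. This stands, and it is why no effect size can be claimed. It does not remove the definition the article does state.
- **The obstruction figures are not forecasts for this trial.** One pair is long term while the leak endpoint is at 6 months; the other is from a small study without significant differences. This stands: they support a likely direction, not a 6-month excess.
- **A sensitive definition suits the aim of not missing leaks without a stoma.** This is fair, and it is a reason to keep the broad count alongside a narrower one and not to impose the narrower one on the safety review, where it would make the threshold harder to reach in the arm at risk.
- **The impact is limited.** Leak is secondary, and an obstructed patient already counts under the primary endpoint of any complication. This stands.

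A reader might infer that excess obstruction pushes the trial towards the 15% threshold. The documents do not support that: the reported excess is in the ileostomy arm, while the threshold is read only in the no-ileostomy arm.

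A reader might also quantify the threshold effect. From a true rate of 10%, with 40% of leak-free patients scanned and 10-20% of those scans showing an isolated sign, the observed rate is 10 + 0.9 x 40 x (0.1 to 0.2) = 13.6-17.2%, and the chance of at least 15 of 97 rises from 0.059 to 0.338-0.715. All three inputs are assumed, and at 17.1% the chance is 0.71 with no misclassification, so this contrast reflects the chosen baseline at least as much as the definition.

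Nor do the documents show that the published 8 to 16% rates used a narrower definition.

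**Conclusion.** The concern holds as a flaw in a stated definition: isolated pelvic free fluid or infiltration scores as a leak, and nothing in the article narrows this.

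For the between-arm comparison, the likely bias raises the ileostomy arm's rate and could hide a true excess without ileostomy. The 1.5-7.0 points are an illustration resting on the assumed 10% leak rate, the assumed 20-60% share and borrowed obstruction rates. The direction rests on those rates carrying over to 6 months.

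For the safety threshold, non-specific findings in the no-ileostomy arm count only if the Endpoints definition applies there, which the article does not say, and no size can be given. This is an inexpensive improvement to a secondary endpoint; it does not undermine the primary analysis.

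**What to change.** 1. Record each CT sign separately in the eCRF, together with contrast extravasation, documented pelvic sepsis and any demonstrated anastomotic defect.
2. Report isolated free fluid or infiltration, meaning without abscess, extradigestive air, extravasation, documented sepsis or a demonstrated defect, as its own category.
3. Give the between-arm leak comparison twice: without that category, and with the present broad definition.
4. Reconcile Endpoints and Patient safety by stating which leak definition the safety committee uses. This point does not argue for either one.

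The cost is a revised endpoint sentence, a few eCRF fields and one additional analysis. The downside is that a few contained leaks may fall into the separate category; the broad-definition analysis retains them.

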#### Data collection and monitoring

An electronic Case Report Form (eCRF) will collect the patients’ baseline data (sociodemographics, such as current age, age at UC diagnosis, sex, body mass index, weight gain since subtotal colectomy, ASA score, and smoking status; medical history, such as extent of UC, associated primary sclerosing cholangitis, and associated comorbidities; surgical history, such as indications for primary STC, delay between STC and IPAA, postoperative course of subtotal colectomy, and history of other surgical procedures; current and previous treatments, such as anti-TNF, immunosuppressive treatment, and corticosteroid therapy; and baseline QoL assessment, using CGQL and EQ-5D-5 L) as well as perioperative, short- and long-term data according to the abovementioned endpoints. Each patient will participate in the study for 15 months (as there are 12-month data collect points from continuity restoration, which is performed up to 3 months after IPAA in case of defunctioning ileostomy). Clinical reviews will be performed one and 6 months after IPAA and 3 and 12 months after continuity restoration (i.e., either IPAA or stoma closure).

Monitoring will be conducted to ensure that the data are accurate/complete, the safety and rights of subjects are being protected, and the study is conducted in accordance with the applicable regulatory requirements. No deidentified individual clinical trial participant-level data (IPD) will be shared. This monitoring (including data management and data quality insurance) will be ensured by the sponsor. The following monitoring will be conducted: informed consent, deviation of protocol, data collection, and safety and rights of participants. All the eCRFs will be routed to the coordinating center, APHM ([name]). Data entry will be performed using REDCap. Quality assurance will be performed from the final database (data manager). The database will be forward to the statistical team (Aix-Marseille Univ, APHM, Clinic Research Platform). The study information of this protocol has been posted on clinicaltrials.gov. The status of this trial is pending: the first inclusion is estimated for September 1st^,^ 2019.

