Currently, there is no quality evidence-based medicine concerning the role of the diverting ileostomy for IPAA: the current practice is guided by the data on proctectomy and coloanal anastomosis in rectal cancer. Namely, defunctioning ileostomy reduces the rate of anastomotic leakage and the severity of fistulas after low colorectal or coloanal anastomosis in rectal cancer [22]. Several prospective randomized controlled trials (RCTs) and meta-analyses have confirmed this observation, and thus far, a defunctioning stoma is mandatory after rectal cancer resection with low anastomosis for a usual period of 6 to 8 weeks [23]. Likewise, the majority of IBD patients undergoing completion proctectomy with IPAA also have a temporary defunctioning ileostomy, i.e., undergo a three-stage IPAA, as recommended by the third ECCO consensus [24]. However, patients presenting with UC or IBDU are different from those presenting with rectal cancer: patients with UC or IBDU are usually younger, rarely have a history of pelvic radiotherapy, and usually do not undergo total mesorectal excision.

Except for the underpowered RCT of Grobler et al., only retrospective and nonrandomized studies have assessed defunctioning ileostomy in IPAA, with the inherent risk of multiple biases [7, 8, 13]. Hence, despite encouraging results, the level of evidence is too low to commonly adopt ileostomy omission in IPAA. Moreover, no studies specifically addressed the question of defunctioning ileostomy during completion proctectomy, even though it concerns 36 to 42% of patients undergoing IPAA [7, 17]. The IDEAL study would be the first to assess the role of defunctioning ileostomy during completion proctectomy with IPAA, where the risk of anastomotic leakage is lower and the benefit of defunctioning ileostomy is more questionable. Indeed, completion proctectomy is mostly performed for patients free of corticosteroid medication and in sufficient nutritional status. It would also be the first trial to assess the economic costs of defunctioning ileostomy, as well as its impact on patient QoL. This is of importance as ileostomy creation is always a major fear for patients presenting with UC or IBDU. Finally, balancing patient safety with health-related QoL, hospital LOS and associated costs is critically important for young adults presenting with a life-long colonic affliction.

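### EQ-5D-5L and CGQL are not measured in either arm between surgery and 3 months after continuity restoration, so no value is taken under the diverting stoma and QALYs must be interpolated across it

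*Protocol article*

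**What the plan says.** Under Endpoints, CGQL and EQ-5D-5L are collected "at baseline and 3 and 12 months from continuity restoration (i.e., either IPAA or ileostomy closure"). Data collection and monitoring lists a "baseline QoL assessment, using CGQL and EQ-5D-5 L" and sets the visits: "Clinical reviews will be performed one and 6 months after IPAA and 3 and 12 months after continuity restoration". It attaches no quality-of-life instrument to the 1-month or 6-month review. Intervention fixes the length of the stoma period: "Ileostomy closure will be performed 6 to 12 weeks after IPAA as per local protocol or later in case of pelvic sepsis".

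Three other places say what these data are for:
- The Background associates the ileostomy with "negative psychological impacts and a poor quality of life (QoL) before closure".
- The Discussion says of the trial: "It would also be the first trial to assess the economic costs of defunctioning ileostomy, as well as its impact on patient QoL".
- Economic assessment derives utilities from EQ-5D-5L. It states a 12-month horizon intended to cover immediate consequences, and describes effectiveness data over that period as precisely collected.

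Endpoints places the cost-utility analysis 12 months from continuity restoration. It times the primary endpoint from the completion proctectomy, so that the time point is the same in both groups.

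**The concern.** The protocol expects the diverting stoma to harm quality of life while it is present. The control arm's questionnaires are timed so that none falls in that interval: one precedes the stoma and two follow its removal. Later closure pushes the questionnaires later, so the longest stoma periods are also unobserved. The experimental arm has its own gap, from surgery to 3 months, when a new undiverted pouch is first in use.

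A QALY is an area under a utility curve. Here the part of the curve where the strategies differ most would be drawn as a straight line between points outside it. Utilities not collected at the time cannot be recovered by later analysis. The clock also matters. Measuring from continuity restoration places the arms' utility values at different times from IPAA, while the economic analysis states a single 12-month horizon.

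**Working it through.** **Inputs from the protocol.** Questionnaires at baseline and at 3 and 12 months after restoration (Endpoints). Closure at 6 to 12 weeks (Intervention). Reviews at 1 and 6 months after IPAA (Data collection and monitoring). Conversion: 52.1775 weeks per year, so 4.348 weeks per month; 3 months is about 13 weeks.

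**The plan's own figure.** "Each patient will participate in the study for 15 months": 12 months after restoration + up to 3 months to closure = 15. This reproduces and confirms that the control clock starts at closure.

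**Timing from IPAA.**

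| | Experimental | Control, closure at 6 weeks | Control, closure at 12 weeks |
|---|---|---|---|
| Restoration | 0 | 6/4.348 = 1.38 months | 12/4.348 = 2.76 months |
| '3-month' value | 3 months (13 weeks) | 4.38 months (6 + 13 = 19 weeks) | 5.76 months (12 + 13 = 25 weeks) |
| '12-month' value | 12 months | 13.38 months | 14.76 months |
| Stoma period / 12 months | none | 1.38/12 = 11.5% | 2.76/12 = 23.0% |

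None of the three planned measurements falls in the stoma period. The 1-month review, at about 4.3 weeks, precedes the earliest planned closure at 6 weeks.

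**Control-arm QALY error (all utilities assumed).** If on-stoma utility lies d below the interpolated line for w weeks, the missed loss is d × w/52.18:
- 0.05 × 6/52.18 = 0.006
- 0.15 × 12/52.18 = 0.035

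That is a shortfall multiplied by time. The fuller quantity is interpolated minus true area from IPAA to 3 months after closure. Let c = w/52.18 years, and let u0, us and u3 be the utilities at baseline, on the stoma and 3 months after closure. With linear recovery after closure:

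error = (u0 + u3)/2 × (c + 0.25) − [us × c + (us + u3)/2 × 0.25]

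| u0, us, u3 | 6 weeks | 12 weeks |
|---|---|---|
| 0.80, 0.70, 0.85 | 0.3011 − 0.2742 = +0.027 | 0.3960 − 0.3547 = +0.041 |
| 0.70, 0.70, 0.85 | 0.2829 − 0.2742 = +0.009 | 0.3720 − 0.3547 = +0.017 |
| 0.65, 0.75, 0.80 | 0.2646 − 0.2800 = −0.015 | 0.3480 − 0.3662 = −0.018 |

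A positive error overstates control QALYs. The third row shows that the sign can reverse if baseline is worse than life with the diverting stoma.

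**Both arms together.** The grid was u0 0.65–0.80, us 0.60–0.75 and u3 0.80–0.90, with immediate or linear recovery, and early-pouch utility 0.70–0.90 for 4 or 8 weeks in the experimental arm followed by a linear move to u3. The error in the between-arm difference (experimental minus control) runs from −0.068 to +0.037 QALY for closure at 6 weeks and from −0.095 to +0.035 at 12 weeks. Two extremes at 6 weeks:
- u0 0.80, us 0.60, u3 0.80, linear recovery, early pouch 0.90 for 8 weeks: experimental error −0.020, control error +0.048, difference −0.068.
- u0 0.65, us 0.75, u3 0.90, immediate recovery, early pouch 0.70 for 8 weeks: experimental error +0.009, control error −0.028, difference +0.037.

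Most combinations are negative, meaning the benefit of omitting the ileostomy is understated. Shares of an arbitrary grid are not probabilities.

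**The case against.** Four points on the other side carry weight.

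*Baseline is not stoma-free.* A reader might infer that baseline precedes any stoma. The Background says subtotal colectomy leaves an end or double-end stoma, so baseline normally reflects life with one, and interpolation from it carries some stoma decrement. This stands, and it limits the size of the error. But baseline is common to both arms and precedes the diverting loop, so it cannot show the loop's effect.

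*Timing from restoration is a legitimate choice.* It compares the arms after equal time with a working pouch, which suits the functional score and pouch-related quality of life. Timing everything from IPAA would give controls less pouch experience. One might read the 6 to 12 extra weeks (6/13 = 46% to 12/13 = 92%) as an unfair recovery advantage for controls. That uses the proctectomy clock alone, and the protocol does not support calling the anchor an error. It is unsuitable only for QALYs over one horizon.

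*The aims may be narrower.* The abstract's objective is quality of life at 12 months, and the Discussion's phrase "as well as its impact on patient QoL" does not itself promise an on-stoma measurement. That is fair. The economic section's claim to cover immediate consequences is harder to reconcile with the schedule.

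*Other stoma-period data are collected.* Complications, readmissions and length of stay are captured, and the primary endpoint is timed from proctectomy. This stands and confines the point to secondary results.

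**Conclusion.** The point holds as a design weakness in the secondary quality-of-life and cost-utility analyses. The stated schedule contains no EQ-5D-5L or CGQL value under the diverting stoma and none in the first weeks of undiverted pouch use. The utility measurements in the two arms are 1.4 to 2.8 months apart on the IPAA clock.

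The unobserved stoma period is 11.5% to 23% of a 12-month horizon for closure on schedule, and longer if closure is delayed. Control QALYs are overstated by about 0.006 to 0.035 per patient if on-stoma utility lies 0.05 to 0.15 below the interpolated line. That direction is plausible from the Background's account, but the figures are assumptions and exclude error in the other arm.

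A reader might go further and conclude that the QALY comparison is certainly biased in favour of the ileostomy arm. The protocol gives no utilities, and the two-arm range above includes both signs, so that is not established. Nothing here affects the primary endpoint.

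**What to change.** Add EQ-5D-5L and CGQL to the 1-month post-IPAA review already scheduled in both arms. For controls closed on schedule this gives one value with the diverting stoma in place, and a matching experimental value in early pouch use. It will mix stoma burden with early surgical recovery, which the between-arm contrast helps to separate. A few controls may have had early closure, which the Study population section contemplates, so stoma status should be recorded with the questionnaire.

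State that QALYs are computed by area under the curve over one window common to both arms, starting at IPAA or randomization. Keep the questionnaires at 3 and 12 months after restoration for pouch-related quality of life. A 6-month questionnaire is optional: at about 26 weeks it falls only 1 week after the existing value for closure at 12 weeks (25 weeks), and 7 weeks after it for closure at 6 weeks (19 weeks).

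The cost is one short additional questionnaire session per patient at an existing visit, and a protocol amendment. It helps only patients who have not yet passed their 1-month review, so it should be made early.
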